### Duration and Follow-Up Surveys

The intervention will run for a period of 2 years. We will conduct four outcome assessments during baseline as well as 6, 12, and 24 months into the intervention.

### Ethical Concerns

The study faces two ethical concerns. First, we need to access patient medical records to monitor health indicators. We need to gain participant consent and have to ensure that confidentiality is protected during the period of the study. Only the health personnel and the local enumerators will know the individuals. In the dataset, all patient information will be anonymous and only linked to the participant's identification number that is given in the context of the study. No identity information will be disclosed. Second, as evident in the examples provided above, in order to prevent negative social stigma, the reminders do not disclose a participant's seropositive status. Participants will be informed of the possibility that texts could be read by other individuals who have access to their phone and they will have to consent to this risk in order to participate in the study.

All relevant ethical clearance from the national ethics committee has been obtained (N° 2014-12-144).

### Implementation of the Text Message Reminder System

The local telecommunication company EVOLE provides a computerized platform for sending the SMS text message reminders, re-launching text messages if delivery fails, and monitoring message receipt. The messages are sent in bulk and a record is kept of all communication. The computerized platform allows us to verify whether the text and image messages have been sent and that the intervention has been properly implemented. We will also use the monitoring data to analyze the quality of the SMS text message communication.

Details about the study design, facility selection, and patient eligibility including the random allocation mechanism, the intervention and the outcome variables are graphically presented in Figure 2.

**Figure 2 figure2:**
[figure not shown]
Study flow.

### Study Measures

#### Primary Outcomes

The study focuses on the measurement of three primary outcomes: retention in care, adherence to ART, and disease progression. Retention is measured by a dichotomous variable-whether a patient remains on ART 6, 12, and 24 months after the intervention has started as compared with baseline [46,47]. Retention could have been conceptualized also as the incidence or number of missed visits during a given reference period [48]. However, remaining in care is in itself an important challenge in Burkina Faso. This is in stark contrast to the situation of PLHIV in developed countries. Therefore, we decided to choose remaining on an ART regimen as our retention measure. Adherence or rather lack of adherence to ART is evaluated as the number of doses missed in the past 7 days, which is a self-reported measure [49-51]. It may have been better to use actual pharmacy dispensing data to calculate a medication possession ratio. However, our field experience suggested that it was not always feasible to obtain detailed and correct information about pharmacy dispensing. Contrary to developed countries where standards across hospitals may be similar, in Burkina Faso we observed considerable differences in the standards and routines across health centers both between regions and within them. Because we assess a wide-scale intervention our study also includes rural and remote areas, which are perhaps even less capable of providing this information. Therefore, we opted for inclusiveness knowing that this implies adjustments in the type of comparable indicators that can be collected and analyzed across health centers [51]. Lastly, disease progression is analyzed using patients’ CD4 counts.

Information on these primary outcomes will be collected using individual questionnaires and patient medical records. Table 2 presents details about the indicators with information about the date of data collection.

**Table 2 table2:** Primary and secondary outcome variables.

Classification		Indicators/measures	Baseline	Follow-ups (months after)		
				6	12	24

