**Results:**

The targeted 3800 patients were recruited between February 2015 and May 2015. But political uncertainty delayed the launch of the intervention until October 2015. Data analysis has not yet started. The first follow-up data collection started in April 2016. To the best of our knowledge, this is the first research that explores the effects of mobile message reminders using a wide-spread sample across an entire nation over a 2-year horizon, especially in a Francophone African country.

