## Introduction

### Background

Several factors inhibit retention in care and adherence to antiretroviral therapy (ART) among people living with human immunodeficiency virus (PLHIV). Typical reasons include individual and social obstacles, such as lack of information on treatment procedures, social stigma, discrimination, and competing priorities that prevent patients from considering antiretroviral treatment as a worthwhile investment of time, energy, or resources [1,2]. In developing countries, economic and contextual barriers may further amplify these challenges because patients are resource-constrained and health facilities may not be easily accessible leading to substantial costs in terms of wage losses and travel expenses [3].

Discontinuation of ART regimens is particularly prevalent in Sub-Saharan Africa. Systematic reviews have found that approximately 22.5% of patients discontinue ART within 10 months and 56% are lost to follow-up or death during the first 2 years of the treatment [4,5]. HIV patients are perhaps not fully aware of the long-term consequences of dropping out from ART treatment. Lack of retention in care and adherence to antiretroviral therapy increases HIV viral loads and the probability of transmission, reduces the number of T-lymphocytes cells in the blood (CD4 count)-an indicator of how well the immune system is working and a strong predictor of HIV progression-leads to deterioration in the quality of life and can be responsible for creating virus strains that are resistant to current HIV medication [6-9]. Favorable health outcomes for PLHIV require lifelong compliance with ART programs. At the macro-level the negative side effects of poor compliance with ART can deteriorate the efficiency and efficacy of public health care systems by increasing the burden of the disease and the potential costs of care in the future [10-12].

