### Study Design

The study design rests on a five-arm, randomized, controlled trial with four treatment arms and one control group. With the support of the Burkinabe Ministry of Health and local health centers, HIV patients have been screened and recruited at 80 health care facilities that provide antiretroviral therapy across the 13 regions of Burkina Faso. Using a 7:7:7:7:10 allocation ratio, patients are randomized to one of the five-arms with the control group being slightly oversampled as we introduce two types of control groups; a control group of patients drawn from health centers which do not receive any of the interventions and a spillover-prone control group drawn from health centers which are visited by both treated and untreated patients. A member of the international survey team carried out the randomization in Stata. The team member did not have any interactions with patients. Once patients were randomly allocated, the intervention was launched and the SMS messages are sent. Patients in each of the five groups receive the public standard care but only four groups receive an SMS reminder that varies by the type of message (text versus American standard code for information interchange (ASCII) image) and its frequency (weekly vs semiweekly). The study collaborates with the health care personnel attending to the patients as well as the associations and self-help groups that provide psychosocial support to PLHIV. The former provide medical information and the latter carry out the survey interviews. The health personnel and the enumerators are not informed about the outcome of the random allocation of the participants. Because they do not know which patient is in which group, we do not expect bias. The study will keep track of the patients 6, 12, and 24 months after the intervention is launched.

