### Randomization

Randomization was undertaken after the collection of the baseline data. As a first step we randomly identified 8 pure control health centers using the random number generator in Excel. These pure control centers allow us to assess whether there are within health center spillovers from those who receive reminders and those who do not. Across the 72 remaining health centers, we randomly assign individuals to 1 of 5 groups (ie, 1 of 4 treatment packages or the control group of patients who do not receive any text message). Due to the potentially large heterogeneity of patient socioeconomic profiles and variations across health centers, the study applies covariate balancing across multiple baseline covariates to minimize imbalance between treatment groups. To increase statistical power and the precision of the results, participants are ordered along key characteristics and randomized within these ordered blocks. The following characteristics are included in the ordering: gender, age and weight of the participant, duration under antiretroviral treatment, health center identifiers, the reported distance to the health center, CD4 counts, and subjective health rating. Following this 2-step procedure, participants are randomly assigned to 1 of 5 groups (4 of which receive various packages of SMS reminders and a control group, which does not). Thus, there are 2 control groups. One control group consists of individuals who do not receive messages but are affiliated to health centers where others receive messages and a pure control group, which consists of individuals who do not receive messages and are affiliated to the 8 pure control health centers where no one receives a message. The introduction of 2 types of control groups is motivated by a desire to address potential spillovers/contamination between treated persons (those who receive a SMS text message) and patients in the control group (those who don’t receive the SMS text message) but frequent the same health center. We know that medical interventions such as deworming and cancer screenings have spillovers [41,42], similarly voter awareness and cash transfer programs have spillovers to untreated but close populations [43,44]. Having 2 control groups allows us to address whether both treated and untreated patients in the treatment health centers are covered by the intervention [43]. In the analysis, we will introduce a dichotomous variable for control patients from mixed-treatment control sites to assess whether their outcomes differ compared with patients from pure control sites who are unlikely to experience spillovers.

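### Retention is timed from the October 2015 launch but referenced to a baseline 5 to 8 months older, so losses before the first message dilute the effect on the risk-difference and odds-ratio scales

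*Protocol article*

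**What the plan says.** All references are to the protocol article.

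- **Definition** (Primary Outcomes): retention is a yes/no variable, "whether a patient remains on ART 6, 12, and 24 months after the intervention has started as compared with baseline". The clock starts at launch; the reference status is baseline.
- **Dates** (Abstract, Results): "The targeted 3800 patients were recruited between February 2015 and May 2015", while "political uncertainty delayed the launch of the intervention until October 2015".
- **Sequence**: "Randomization was undertaken after the collection of the baseline data" (Randomization), and "Once patients were randomly allocated, the intervention was launched and the SMS messages are sent" (Study Design). No randomisation date is given.
- **Assessments** (Duration and Follow-Up Surveys): "We will conduct four outcome assessments during baseline as well as 6, 12, and 24 months into the intervention". None falls at launch.
- **Analysis** (Analysis Plan): retention is modelled by Logit. Message fatigue is judged partly by how the effect on the primary outcomes changes between survey rounds (Secondary Outcomes), and the Abstract expects a short-run benefit that may fade.
- **Status** (Results): the delay is reported, the analysis has not begun, and the authors still intend to follow the plan as written.

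**The concern.** With a launch soon after baseline, the two time origins would nearly coincide. The delay separated them, and the retention definition was not adapted. A patient who died or left care in, say, July 2015 received no message while in care, yet scores as not retained at 6, 12 and 24 months in whichever arm they were assigned to.

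Such failures arise in all arms alike in expectation. They carry no information on the messages, but they enlarge the failure count on which the odds ratio depends. Their share is largest at 6 months, the wave that speaks most directly to a short-run benefit, and it falls at later waves. At stake are the power of the primary retention comparison and the reading of the effect's time course.

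**Working it through.** **Plan's own figure.** There is none to reproduce. The 3800 is sized on adherence (65% to 70%), and no power is stated for retention. This point does not depend on the 3800.

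**Gap.** May to October is 5 months and February to October is 8. The 6-, 12- and 24-month outcomes therefore span about 11–14, 17–20 and 29–32 months from baseline. That baseline data were taken at recruitment is inferred from the Recruitment and Randomization sections.

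**Pre-launch loss q.** Assume a constant hazard h, so q = 1 − exp(−h × gap).

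- Regional reviews (Background): "approximately 22.5% of patients discontinue ART within 10 months and 56% are lost to follow-up or death during the first 2 years". From the first figure, h = −ln(0.775)/10 = 0.0255 per month, giving q = 12.0% (5 months) to 18.4% (8 months). From the second, h = −ln(0.44)/24 = 0.0342, giving 15.7% to 23.9%.
- National figure (Trial Setting): 443 lost in 2014 against 46,623 on ART, about 0.95% a year, giving q = 0.4% to 0.6%.

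**Effect on each scale.** Let S0 and S1 be retention among patients on ART at launch (control, SMS), and G = 1 − q. With no return to care, the baseline-anchored proportions are G·S0 and G·S1. Hence:

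- ratio: G·S1 / G·S0 = S1/S0, unchanged;
- risk difference: G(S1 − S0), multiplied by (1 − q) at every wave;
- odds ratio: pulled towards 1;
- pre-launch share of control failures: (1 − G)/(1 − G·S0).

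**Illustration.** Assumptions: h = 0.0255, mid-gap 6.5 months (G = exp(−6.5h) = 0.847), constant hazard ratio 0.8 after launch, S0 = exp(−ht), S1 = exp(−0.8ht).

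| | 6 months | 12 months | 24 months |
|---|---|---|---|
| S0, S1 | 0.858, 0.885 | 0.737, 0.783 | 0.542, 0.613 |
| Pre-launch share of control failures | 56% | 41% | 28% |
| Odds ratio, launch-anchored | 1.27 | 1.29 | 1.34 |
| Odds ratio, baseline-anchored | 1.12 | 1.19 | 1.27 |
| Risk difference (points), launch-anchored | 2.67 | 4.65 | 7.06 |
| Risk difference (points), baseline-anchored | 2.26 | 3.94 | 5.98 |
| Retention ratio, either definition | 1.031 | 1.063 | 1.130 |

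**Power.** Pooled SMS 2800 against control 1000 (the 7:7:7:7:10 ratio at 3800), two-sided alpha 0.05/3 = 0.0167, unpooled normal approximation, no clustering or covariates; the launch-anchored set has G times as many patients. Baseline-anchored against launch-anchored: 16% against 33% at 6 months, and 43% against 61% at 12.

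**Dependence on q.** Fix instead an assumed 77.5% against 82.5% retention among those on ART at launch (alpha 0.05, same group sizes, variance pooled under the null):

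- q = 0.12: difference 5.0 → 4.4 points, odds ratio 1.37 → 1.24, power 75% against 89% in the restricted set;
- q = 0.184: difference 4.1 points, odds ratio 1.20, power 65% against 87%;
- q = 0.006: power 92% against 92.5%.

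Under the constant-hazard model with hazard ratio 0.8, the odds ratio is distorted even at the national rate (6 months: 1.11 against 1.25; 24 months: 1.19 against 1.25). The differences there are about 0.1 point at 6 months and 0.4 at 24, so little practical information is at stake.

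**The case against.** Several points on the other side stand.

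- **Validity.** A reader might infer that the comparison is biased. It is not: losses before any message are non-differential, and the test under no effect is intact.
- **Fade-out.** A reader might infer that the delay hides fade-out in general. The table shows otherwise: the ratio is unaffected and the risk difference is scaled by the same 0.847 at each wave, so its time profile keeps its shape. Only the odds ratio's slope is distorted. The launch-anchored odds ratio also rises somewhat under a constant hazard ratio. The plan includes simple group comparisons and difference-in-difference besides the Logit.
- **Size.** The review figures are regional and describe patients early in treatment, whereas this sample includes experienced patients. The national figure makes q negligible. Yet that figure may undercount: the article attributes all those losses to deaths, and it aims for at least two-thirds of the sample to have under 4 years on ART because drop-out is highest among initiators. The documents cannot settle q.
- **Return to care.** Nothing makes sending conditional on attendance. A patient who lapsed before launch and resumed after reminders would count as retained, so not every early leaver is a fixed failure, and the model above overstates the dilution to that extent.
- **Changing the primary population.** A reader might conclude that primary retention must be restricted to patients on ART at launch. The article itself reports uneven pharmacy information and routines across centres, so launch status set retrospectively could be incomplete. Replacing the all-randomised set is debatable.
- **Randomisation date.** The article does not say whether known deaths or departures were removed before allocation. If they were, q is smaller.

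None of this removes the mismatch between the two time origins.

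**Conclusion.** The concern holds as attenuation and lost power, with a scale-dependent distortion of the time trend. The timing and the definition come straight from the article. The direction follows by algebra if most pre-launch leavers stay out of care. The (1 − q) multiplier on the risk difference lies between 0.994–0.996 (national figure) and 0.82–0.88 (10-month review figure), or 0.76–0.84 on the two-year review figure. At the low end the power loss is negligible; at the high end 6-month power roughly halves in the illustration. The odds ratios and powers rest on a constant hazard, an assumed hazard ratio of 0.8, no return to care and no clustering, so they show mechanism and order of magnitude and are not forecasts. A change is worthwhile because the fatigue question depends on comparing effects across waves and the planned model for retention yields odds ratios.

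**What to change.** Before analysis starts:

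1. Keep the all-randomised, baseline-anchored comparison.
2. Pre-specify beside it a launch-anchored retention analysis: on ART at 6, 12 and 24 months among randomised patients alive and on ART at the October 2015 launch. Take launch status from the medical records already covered by consent, extracted identically in all arms by staff not told the allocation. No message had been sent by then, so the restriction uses only pre-exposure information.
3. Report deaths and losses between baseline and launch by arm. This gives q directly and checks that it is balanced.
4. Judge fade-out on the launch-anchored set, or on the risk-difference or retention-ratio scale, and not on the baseline-anchored odds ratio alone.

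Cost: one status date per patient from records already being consulted, and some added text. The restricted set has a smaller denominator, some launch statuses must be established in retrospect and may be incomplete, and re-engagement among pre-launch leavers is not captured there; the all-randomised analysis retains it.

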**Primary outcomes**						
	Retention in care	Dichotomous measure whether a patient remains on ART	X	X	X	X
	ART adherence	Number of doses missed in the past 7 days	X	X	X	X
	Disease progression	CD4 count	X	X	X	X
**Secondary outcomes**						
	Health center visits	Incidence and number of missed visits		X	X	X
	Patient health	Biomarker: body mass index	X	X	X	X
		Incidence of coinfection	X	X	X	X
		Mortality	X	X	X	X
		Subjective health rating	X	X	X	X
		Measures of mental health		X		X
	Preferences	Risk preference		X		X
		Subjective discount factor		X		X
	Nutrition		X		X	
	Message type and frequency	Comparison of the four interventions		X	X	X
	Message fatigue	Patients' perceptions of the intervention		X	X	X

#### Secondary Outcomes

Information on 5 groups of secondary outcomes will be collected. First, we will obtain information about the incidence and number of missed health center visits. Second, because we are also interested in more general physical and psychosocial health aspects we will gather information about the body mass index, the incidence of coinfections, mortality, as well as subjective and mental health ratings. In addition, we will collect information on the patients’ levels of risk preference and their subjective discount factors. Third, we will also measure nutritional outcomes. Fourth, to assess design effects and the duration of effectiveness of the mHealth intervention, we will gather data on the message type and frequency. The sensitivity to message type (text vs ASCII image) and the frequency (weekly vs semiweekly) of receiving the messages will be measured by comparing the effects of the 4 different interventions on the primary outcomes [24-30]. Finally, message fatigue will be measured using patients’ perceptions and possible changes in the impact on the primary outcome indicators across follow-up survey rounds. The secondary outcomes will be measured 6, 12, and 24 months after commencement of the intervention.

### Analysis Plan

Our analysis will exploit the randomized nature of the intervention to attribute treatment effects. In addition to a simple comparison between the pooled treatments and the control group we will also assess the differential impact of the 4 treatment arms. We will employ multivariate regression models to assess the impact of the interventions on each of the primary outcome variables. For the continuous outcome measure (CD4 count) we plan to employ an Ordinary Least Squares model. For the count data (pill doses missed) and if the continuous outcome measure is skewed, we propose to make use of a Poisson model; for the dichotomous outcome (remaining on ARV regimen), we propose to employ a Logit model. In all models we will control for the clustering of participants within health centers.

We will make use of the coefficient estimates from the 4 treatment arms to establish a preference ordering of the effectiveness of the different types (text vs ASCII image) and frequencies (weekly vs semiweekly) of the SMS text message reminders. We will also estimate quantile regressions to identify which group(s) of participants are most (least) likely to have gained from the interventions. Comprehensive data on patient characteristics collected at baseline will allow us to control for confounding factors and patient heterogeneity. These patient characteristics include age, gender, ethnicity, education, whether the patient is the head of the household, income, and whether the patient works. The simple comparison of outcome variables across groups will be complemented by a difference-in-difference identification strategy where we jointly employ the data from the three follow-up surveys. This analysis will permit us to tease out the differences in health outcomes attributable to each of the 4 interventions while controlling for time-fixed effects.

The data will be collected and coded by trained enumerators and analyzed using the statistical and data analysis program STATA. We will use conventional levels of significance at 1%, 5%, and 10%. Because we identified three primary outcome variables we will make use of an inflated alpha when determining significance levels for each and every outcome separately. We apply this correction because the more significance tests we conduct at α=0.05, the more likely we are to claim that we have a statistically significant result. For a significance level of 5% the Bonferroni inflated alpha is 0.05/3 = 0.015.

We expect missing data to be below 5% and plan to address it using imputation techniques. However, the technique that we do use will depend on the characteristics of the missing information. Our goal is to avoid reducing the sample size without compromising statistical validity.

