
### Intervention

The intervention comprises 4 treatment groups and 1 control group to investigate the impact of different types of SMS text message reminders sent out at different frequencies on patient outcomes. For groups 1 to 4, messages will be sent on a weekly basis. Patients of each of the 4 treatment groups will receive at least 1 text or image message per week. Image messages are used to ensure that the intervention reaches out to people with limited literacy skills and they will be sent as ASCII pictures. Because we do not expect the participants to have smartphones, we use ASCII images that can be displayed on basic mobile phones. The content and frequency of the messages will vary for each of the 4 treatment groups. While the first treatment group will receive only 1 text message per week (low frequency), the second treatment group receives a total of 2 text messages per week (high frequency). Meanwhile, the third group will get 1 text and 1 image message per week and, the fourth group will receive 2 image messages per week. All messages will be sent at 8 am and patients will not be prompted to respond. The impact of the treatments will be assessed in follow-up surveys at 6, 12, and 24 months after the start of the intervention. A detailed identification of the 5 groups, type of interventions, and timings are presented in Table 1.

**Table 1 table1:** Identification of the five intervention groups.

Treatment arms		Intervention (per week)	Timing

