### Sample Size

Power calculations need to account for the stratified nature of the sample. There are 80 treatment centers. We randomly preserve 8 pure control centers to assess spillovers. Within each of the remaining 72 centers, treated and untreated participants are sampled. Thus, for the majority of the centers treatment allocation is not at the level of the center but at the level of the individual. The sample size is calculated with the clustersampsi command of Stata, Version 13 assuming a power of 80% and a significance level of 5%. Furthermore, we impose an intraclass correlation coefficient of 0.015 to quantify the degree to which patients within the same health center are related [45]. We allow for cluster sizes to vary because we know that the size of the eligible population varies across clusters. Thus, we impose a coefficient of variation of cluster sizes of 0.5 (ratio of the standard deviation of cluster sizes to the mean cluster size). Because we collect baseline information we can control for observable characteristics and their correlation with the outcome. We impose a correlation of 0.85. Lastly, because we expect that 35% of the patients will forget to take antiretroviral (ARV) medication from time to time, a target sample size of 3800 PLHIV is needed to obtain a “minimum detectable effect” of an increase in adherence from 65% to 70%. These adherence figures are based on a reported 67% adherence among female PLHIV in Burkina and the government target to bring adherence up to at least 80% [37,38]. As we are conservative about the possibilities of mHealth to raise adherence by 15% the sample was set up in such a way to also identify small gains.

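### The plan ranks the four message packages by their coefficients with no stated between-arm comparison, so it can name a best package by chance, and one ranking over these four arms is neither a type effect nor a frequency effect

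*Protocol article*

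**What the plan says.** The Analysis Plan turns the four arm estimates into a ranking: "We will make use of the coefficient estimates from the 4 treatment arms to establish a preference ordering of the effectiveness" of the types (text or ASCII image) and frequencies (weekly or semiweekly). Secondary Outcomes describes the same comparison: sensitivity to type and frequency "will be measured by comparing the effects of the 4 different interventions on the primary outcomes".

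The Analysis Plan also promises to assess how the four arms differ, lists significance levels of 1%, 5% and 10%, and adds a difference-in-difference analysis. Its alpha correction is for the three primary outcomes. It does not mention the four arms or the three follow-up waves, and it does not say which outcome or wave decides the order.

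The arms, from the Intervention section and Table 1, are:
- Treatment 1: one text per week.
- Treatment 2: two texts per week.
- Treatment 3: "the third group will get 1 text and 1 image message per week".
- Treatment 4: images only. The Intervention text gives two per week; Table 1 gives one message, every Monday.

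Study Design gives the arm sizes: "Using a 7:7:7:7:10 allocation ratio, patients are randomized to one of the five-arms". The Sample Size section plans for adherence of 65% against 70% and states no target for a difference between two message arms.

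**The concern.** An ordering built from coefficients always has a first place. If the packages do not differ, sampling error decides which one leads, and the leader's apparent advantage is inflated because it was picked for being largest. Nothing printed makes the ordering depend on whether the arms can be told apart.

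The second difficulty is what the ordering would mean. The four arms do not cross type with frequency. A position in a four-way list reflects message type, weekly number and mixture together, so the list cannot be read as text against image or as once against twice a week.

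Comparing type and frequency is a stated objective, and the Discussion expects the conclusions to feed recommendations and guidelines. A package could be recommended that is no better than the other three.

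**Working it through.** **Inputs from the protocol.** Total 3800 (Sample Size); ratio 7:7:7:7:10 (Study Design); adherence 65% against 70%, 80% power, 5% significance, intraclass correlation 0.015, coefficient of variation of cluster size 0.5, baseline correlation 0.85 (Sample Size); 80 centers, 72 of them randomized by individual (Randomization).

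**Assumptions.** Two-sided tests; 3800 split exactly by the ratio; no attrition; adherence as a proportion at one time point; baseline correlation r between 0 and 0.85. The true gaps between arms used below are also assumptions.

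**1. The plan's own figure.** Comparing 65% with 70% needs 1377 per arm. With a mean cluster size of 3800/80 = 47.5, the design effect is 1 + ((1 + 0.5²) × 47.5 − 1) × 0.015 = 1.876. The variance factor for r = 0.85 is 1 − 0.85² = 0.2775. Then 1377 × 1.876 × 0.2775 ≈ 717 per arm, or 15.1 clusters. Rounding up gives 16 × 47.5 = 760 per arm, and 5 × 760 = 3800. The match needs five equal arms, whole-cluster rounding and a cluster size taken from 3800 itself; unrounded, the total is 3584. The calculation sizes an arm for the 5-point effect and leans heavily on r = 0.85.

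**2. Precision of an arm-to-arm difference.** The four message arms are randomized by individual within centers, so no design effect is applied.
- Per arm: 3800 × 7/38 = 700.
- r = 0: SE of one arm = √(0.7 × 0.3/700) = 1.73 points; of a difference, 1.73 × √2 = 2.45 points.
- r = 0.85: multiply by √0.2775 = 0.527, giving 0.91 and 1.29 points.

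**3. All four arms equal** (400,000 simulated sets of four normal estimates).

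| | r = 0 | r = 0.85 |
|---|---|---|
| Expected best-to-worst gap | 3.6 points | 1.9 points |
| Gap as a share of the planned 5 points | 3.6/5 = 72% | 1.9/5 = 38% |
| Some pair at nominal p<0.05 | 20% | 20% |

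**4. Arms truly different.**

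| Assumed truth | r = 0 | r = 0.85 |
|---|---|---|
| Effects 1 point apart: full order right | 19% | 41% |
| One arm 2 points ahead of the rest: ranked first | 60% | 86% |
| One arm 5 points ahead of the rest: ranked first | 95% | over 99% |

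**5. What a formal comparison can detect.** Smallest difference with 80% power = (critical value + 0.84) × SE of the difference.

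| Comparisons | Critical value | r = 0 | r = 0.85 |
|---|---|---|---|
| One pair | 1.96 | 6.9 points | 3.6 points |
| Three contrasts, Bonferroni | 2.39 | 7.9 points | 4.2 points |
| Six pairs, Bonferroni | 2.64 | 8.5 points | 4.5 points |

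Power for 65% against 70% between two message arms is 51% at r = 0 and 97% at r = 0.85 for one pair, and 26% and 88% after correction for six pairs.

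**6. Which pairs isolate a factor.**
- Treatment 2 against Treatment 1: frequency, for text.
- Treatment 3 against Treatment 2: one image in place of one text, at the same weekly number.
- Treatment 4 against a text arm: type, but only if the weekly number matches. That is Treatment 2 under the Intervention text and Treatment 1 under Table 1.
- Frequency for images: no pair, since there is only one image-only arm.

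**The case against.** The strongest reply is that silence is not exclusion. This is a condensed article, the analysis plan may hold the contrasts and intervals, regression output carries standard errors, and the same section promises to assess how the arms differ. It is true that the protocol does not say point estimates alone will decide. But it does fix a use for the coefficients, namely a preference ordering, and nothing printed ties that ordering to an arm comparison. The point is about the rule that is stated.

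A reader might go further and infer that the ranking would be mostly noise. The documents do not support that. It depends on the true gaps, which the protocol does not give, and on the baseline correlation. At the plan's own 0.85, an arm 2 points ahead ranks first 86% of the time.

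A reader might also infer that type and frequency cannot be separated. They can, by the specific pairs listed, and a 2x2 design is not required. What fails is reading one four-arm order as either effect.

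The figures are for a proportion, whereas Study Measures defines adherence as a count of missed doses and the coefficients would come from Poisson, least-squares and logit models. Blocked randomization and joint use of the three follow-ups could also improve precision. That objection stands, so the figures illustrate the problem and do not measure this plan's error. Showing an order of estimates as description is also legitimate.

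**Conclusion.** The concern holds in this limited form. As written, the rule can name a best package by chance: with equal arms it would show an expected best-to-worst gap of 1.9 to 3.6 points, and an uncorrected look at all pairs would find at least one nominal difference about one time in five. These sizes rest on 700 per arm, adherence as a proportion near 70%, one time point, no attrition, and r from 0.85 down to 0. A difference near 5 points between message arms would be detected reliably at r = 0.85, but not at r = 0.

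A single ordering of these four arms does not estimate a type effect or a frequency effect, and image frequency is never varied. Which text arm gives the clean type contrast cannot be settled while the Intervention text and Table 1 disagree on Treatment 4. The comparison is a secondary objective and the primary comparison with control is unaffected, so this should be changed before analysis but does not undermine the trial.

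**What to change.** Reconcile the weekly number of messages for Treatment 4 between the Intervention text and Table 1. Then replace the ordering rule with:

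1. A joint test that the four arm effects are equal.
2. Pre-named contrasts: frequency = Treatment 2 minus Treatment 1; substitution of one image for one text = Treatment 3 minus Treatment 2; type = Treatment 4 minus the text arm with the same weekly frequency.
3. Estimates with confidence intervals adjusted for the comparisons actually used: three for the named contrasts, six if a best package overall is to be claimed.
4. A named outcome and follow-up wave that decide the conclusion.

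An order of the estimates may still be shown descriptively with its intervals. Call a package better only where the adjusted interval excludes zero; otherwise report that the arms could not be separated. State that image frequency is not tested.

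The cost is wording and a few linear contrasts from the regressions already planned. The protocol reports that analysis has not started, so the change is timely. The downside is that the trial may not name a best package.
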